#### Secondary outcomes

The secondary outcomes include changes in blood glucose and blood lipids, assessed using HbA1c, TC, TGs, HDL-C, and LDL-C; activities of daily living, assessed using IADL; exclusion of patients with vascular dementia, assessed using Hachinski Ischemic Scale (HIS); and exclusion of patients with abnormal psychiatric behavior assessed using SAS and SDS.

##### Instrumental Activities of Daily Living Scale (IADL)

This scale may identify incipient decline-physical, cognitive, or both-in an older adult who might otherwise appear capable and healthy. It assesses a person’s ability to perform tasks including telephoning, shopping, food preparation, housekeeping, laundering, use of transportation, use of medicine, and financial behavior [21].

##### Hachinski Ischemic Scale (HIS)

This scale is composed of 13 items, which are derived from clinical practice experience. It needs to be judged by combining the patient’s history, clinical symptoms, signs, and auxiliary examination results. It can be simple, easy, and effective to distinguish vascular dementia from Alzheimer’s disease. HIS ≥ 7 points supports vascular dementia, and ≤ 4 points supports Alzheimer’s disease [22].

##### Self-Rating Anxiety Scale (SAS)

The scale includes 20 entries divided into four grade ratings according to the frequency of anxiety status in the past 7 days. The standard cutoff scores used define < 50 as no anxiety, 50–59 as minimal to mild anxiety, 60–69 as moderate to marked anxiety, and ≥ 70 as severe anxiety [23].

##### Self-rating depression scale (SDS)

The scale includes 20 entries divided into four grade ratings according to the frequency of depression status in the past 7 days. The standard cutoff scores used define < 50 as no depression, 50–59 as minimal to mild depression, 60–69 as moderate to marked depression, and ≥ 70 as severe depression [24].

### Sample size estimation

The sample size was calculated based on the MoCA scale score as the primary outcome. The sample size was calculated based on the noninferiority comparison of the two groups: *α* = 0.025, 1−*β* = 0.80, *Δ* = − 0.1, which was calculated by PASS software with *n* ≈ 24. Because there was partial shedding in the treatment process, the shedding rate was 20%, and thus, it was appropriate to increase the sample size and take *n* = 30 cases per group. Therefore, 30 cases per group were needed, totaling 90 patients in 3 groups.

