### Statistical analysis

#### Clinical data analysis

Statistical analysis of the clinical outcomes will be performed using SPSS 24.0 statistical software. All statistical tests will be bilateral, and *p* < 0.05 will be considered statistically significant. For clinical information, data will be presented as the mean ± standard deviation. Student’s *t* test and the chi-square test will be used to compare group differences at baseline. A paired *t* test will be used to compare the clinical outcomes within the groups. Analysis of variance and the Wilcoxon rank-sum (if normality is violated) will be used to compare the clinical feature changes between groups. The clinical data, including MoCA, CDR, HbA1c, TC, TGs, HDL-C, and LDL-C, will be converted to domain z scores for correlational analysis with imaging data. Missing data for the primary outcome will be imputed using the multiple imputation method.

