In addition, there are no exact and effective drugs or methods for the treatment of DCI in modern medicine, mostly starting from improving symptoms and delaying the disease. On the basis of controlling blood glucose and correcting the disorder of lipid metabolism, drugs to improve the function of brain cells are added for combined treatment, but long-term use easily produces side effects. Related studies have confirmed the important role of acupuncture in the prevention and treatment of diabetes and its complications [13, 27]. However, to date, there have been no properly designed randomized, sham-controlled pilot trials at home or abroad to provide clear evidence to prove the effectiveness of acupuncture in the treatment of DCI and to explain its related mechanism. The intervention method of this study was “Adjust Zang-fu and Arouse Spirit” electroacupuncture therapy, which is based on the previous research results of the research group and the TCM etiology and pathogenesis of DCI. It has the functions of harmonizing Zang-fu organs, freeing *qi* and blood, arousing the brain and regulating spirit. In the early stage, the research group applied this acupuncture method to the clinical treatment of DCI, showing a good clinical effect. At the same time, to eliminate the placebo effect of electroacupuncture, a sham electroacupuncture group was set up, but double-blinding could not be achieved because of the particularity of the electroacupuncture operation.

The main evaluation indicators of this study include brain imaging results and two cognitive assessment scales, and the secondary evaluation indicators include blood glucose and blood lipid detection and four related scales. The time point of evaluation included one evaluation before the treatment period, two evaluations in the treatment period and four evaluations in the follow-up period, for a total of seven evaluations. The brain imaging data of the patients were analyzed at the individual level, and the correlations between the brain imaging, scale results, and test results were analyzed. The purpose of this study was to analyze the changes in brain structure and function in patients with DCI and to explore the therapeutic effect of “Adjust Zang-fu and Arouse Spirit” electroacupuncture on DCI and its correlation with the changes in brain structure and function in patients with DCI.

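### The sample size is justified by a noninferiority comparison that the trial does not test, so the stated 80% power is not established for the planned superiority comparison with sham, and n = 24 does not follow from the stated inputs

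*Protocol article*

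**What the plan says.** In the protocol article, Sample size estimation names the outcome, "The sample size was calculated based on the MoCA scale score as the primary outcome", and then the framework: "The sample size was calculated based on the noninferiority comparison of the two groups". The inputs given are alpha = 0.025, 1 - beta = 0.80 and delta = -0.1, "which was calculated by PASS software with" n of about 24. Then "the shedding rate was 20"%, and the conclusion is that "30 cases per group were needed, totaling 90 patients in 3 groups". The section gives no SD, no expected difference and no unit for delta, and it does not say which two groups are compared.

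No other section speaks of noninferiority. The aims at the end of the Background are to clarify how electroacupuncture prevents and improves cognitive dysfunction. The Discussion explains the comparator: "to eliminate the placebo effect of electroacupuncture, a sham electroacupuncture group was set up". Under Clinical data analysis, "All statistical tests will be bilateral" with p < 0.05 as the threshold, and analysis of variance or a Wilcoxon rank-sum test "will be used to compare the clinical feature changes between groups". No margin and no confidence-bound rule appears there.

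**The concern.** A power figure describes one hypothesis, one test and one assumed truth. Here the hypothesis in the sizing section (not worse than sham by more than 0.1) differs from the one in the aims, the choice of comparator and the analysis (better than sham). Ruling out a deficit of 0.1 does not rule out zero effect. Against a sham of blunt, non-penetrating needles with no current, a noninferiority result would therefore say nothing about efficacy.

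The size itself also looks wrong. A margin of 0.1 on a 30-point scale is very small, and such margins normally lead to very large trials, not to 24 per group.

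This is the article's only justification of its size. As it stands, a null result could be taken to come from a trial with 80% power for the efficacy question, or a claim of noninferiority to sham could be presented as a planned success.

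**Working it through.** **Inputs.** From Sample size estimation: alpha 0.025 (read as one-sided, as is usual for noninferiority), power 0.80, |delta| = 0.1, n of about 24, dropout 20%. The two groups are taken to be electroacupuncture and sham. Assumed because the article does not state them: MoCA SD of 2, 3 or 4 points, and true differences as shown.

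**Dropout step.** 24 / (1 - 0.20) = 30 per group and 3 x 30 = 90. This reproduces.

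**n = 24 with zero true difference.** n per group = 2 x (1.960 + 0.842)^2 x SD^2 / margin^2 = 2 x 7.849 x SD^2 / 0.01.

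| Reading of delta | SD | n per group | Power with 24 per group |
|---|---|---|---|
| 0.1 points | 2 | 6,280 | 3.7% |
| 0.1 points | 3 | 14,128 | 3.3% |
| 0.1 points | 4 | 25,117 | 3.1% |
| 0.1 SD | any | 1,570 | 5.3% |

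Solving backwards, n = 24 needs SD = 0.1 x sqrt(12 / 7.849) = 0.124 points, which is implausible on a 30-point scale. If delta were a difference in proportions with equal true rates, 24 would need rates of about 98%. Rates of 50% and 90% need 393 and 142 per group.

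**n = 24 with an assumed benefit.** n = 2 x 7.849 x SD^2 / (benefit + 0.1)^2.

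| SD | Benefit (points) | Benefit / SD | n per group | Superiority power, 24 per group (two-sided 0.05 t-test) |
|---|---|---|---|---|
| 2 | 1.52 | 0.76 | 23.9 | 73% |
| 3 | 2.33 | 0.78 | 23.9 | 75% |
| 4 | 3.13 | 0.78 | 24.1 | 76% |

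Other routes also give 24. With delta as 0.1 SD and a benefit of 0.71 SD, 2 x 7.849 / 0.81^2 = 23.9. With proportions of 0.60 and 0.85, 7.849 x (0.24 + 0.1275) / 0.35^2 = 23.5, rounded up to 24. None of these benefits or rates is in the article, and proportions do not fit a sizing on the MoCA score.

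**What the size gives for superiority.** Two-sided alpha 0.05, t-test: 80% power is reached at 0.83 SD with 24 evaluable per arm and at 0.74 SD with 30. With 24 per arm, power is about 40% at 0.5 SD and 17% at 0.3 SD. The half-width of the 95% confidence interval for the difference is t x sqrt(2/n): 2.013 x sqrt(2/24) = 0.58 SD with 24, and 2.002 x sqrt(2/30) = 0.52 SD with 30.

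**The case against.** The strongest reply is that the figure cannot be shown to be false. The article gives no SD, expected difference or unit for delta, and a condensed article may leave these to the full protocol. If a benefit was assumed, a noninferiority calculation can return 24. This stands. A reader might infer that n = 24 is impossible, or that it requires an SD of about 0.12 points, but that holds only if the true difference is zero, which the article does not say. The absence of an SD is not in itself the finding.

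A reader might also infer that a treatment no better than sham would pass a noninferiority test 80% of the time. With a 0.1-point margin and SDs of 2 to 4 points it would pass only about 3% to 4% of the time. The valid objection to noninferiority against sham is logical: passing would not show efficacy.

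Nor is alpha a discrepancy, since one-sided 0.025 matches two-sided 0.05. Finally, the article calls the trial a pilot meant to inform later trials, which lowers the stakes of a power statement. It does not excuse stating power for a different hypothesis.

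**Conclusion.** The point holds as a mismatch of hypothesis. It rests on the article's own text and needs no assumed SD: the size is justified by noninferiority, while the aims, the sham comparator and the two-sided tests without a margin pose a superiority question. The stated 80% power is therefore not established for the planned comparison. It would go too far to say that this power does not exist, because 24 evaluable per arm has 80% power for superiority if the true difference is about 0.83 SD.

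The second part holds with its conditions. From the stated inputs alone n = 24 does not follow. With zero true difference it falls short by a factor of about 65 (1,570 / 24, margin 0.1 SD) to over 1,000 (25,117 / 24, margin 0.1 points, SD 4). It is reached only with something unstated, such as a benefit of about 0.76 to 0.78 SD. That is in effect a superiority assumption, and superiority power under it is about 73% to 76%, not 80%. The SDs of 2 to 4 points are assumptions; the results in SD units do not depend on them.

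**What to change.** Delete the noninferiority statement and the margin, keep 30 enrolled per arm, and choose one of two restatements.

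1. Superiority of electroacupuncture over sham on MoCA change, at a primary time point that the sponsor names (the article lists several assessments and singles out none), two-sided alpha 0.05. State that 24 evaluable per arm gives 80% power only for about 0.83 SD (0.74 SD if all 30 are evaluable). Give the SD, the target difference and their source, so that 0.83 SD is not read as a clinically justified target.
2. A pilot size of 30 per arm with no power claim, giving the expected 95% confidence interval half-width: about 0.58 SD with 24 evaluable per arm and 0.52 SD with 30.

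In either case, state that no noninferiority claim against sham will be made. The cost is a change of wording and a less favourable power statement, with no additional patients.

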### Data collecting and monitoring

The Data Monitoring Committee is composed of members of the Medical Ethics Committee of the Third Affiliated Hospital of Changchun University of Traditional Chinese Medicine, and the committee has determined that there is no conflict of interest with this experiment. The data will be recorded on the paper CRFs by the designated result evaluator and double-entered into the electronic CRFs, which are established and monitored by the Medical Ethics Committee of the Third Affiliated Hospital of Changchun University of Traditional Chinese Medicine. A data acquisition and management system was established, including the dual input of data entry personnel and researchers, and checked by a third person to ensure the objectivity, authenticity, and accuracy of the research data. Monitors will audit the data every 3 months. This process will be independent from investigators. Acupuncturists and statisticians will not be able to access the data during the evaluation process. The researcher with the approved proposal will be permitted to access the final dataset by contacting the corresponding authors.

### Statistical analysis

#### Clinical data analysis

Statistical analysis of the clinical outcomes will be performed using SPSS 24.0 statistical software. All statistical tests will be bilateral, and *p* < 0.05 will be considered statistically significant. For clinical information, data will be presented as the mean ± standard deviation. Student’s *t* test and the chi-square test will be used to compare group differences at baseline. A paired *t* test will be used to compare the clinical outcomes within the groups. Analysis of variance and the Wilcoxon rank-sum (if normality is violated) will be used to compare the clinical feature changes between groups. The clinical data, including MoCA, CDR, HbA1c, TC, TGs, HDL-C, and LDL-C, will be converted to domain z scores for correlational analysis with imaging data. Missing data for the primary outcome will be imputed using the multiple imputation method.

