## Methods/design

### Study design

This is a randomized controlled trial. The protocol was approved by the Medical Ethics Committee of the Third Affiliated Hospital of Changchun University of Chinese Medicine (approval No. of ethics committee: CZDSFYLL2020-001-01) and registered at the Chinese Clinical Trial Registry (registration number: ChiCTR2000040268, protocol version number: V3.0, 02 October 2020.).

In this study, the tested patients will be randomly divided into two groups: an intervention group and a control group. Patients who meet the inclusion and exclusion criteria will first complete informed consent and then be randomized and stratified according to the clinical treatment. The intervention group will be divided into the “Adjust Zang-fu and Arouse Spirit” electroacupuncture group, which will be treated with electroacupuncture on a fixed prescription of acupoints, and the sham electroacupuncture group, which will be treated with electroacupuncture on nonacupuncture points and a sham instrument.

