### Participants

We will recruit 90 participants from the third Affiliated Hospital of Changchun University of Chinese Medicine (Changchun, China). Before treatment, we will perform glycosylated hemoglobin A1 (HbA1c) tests, blood lipid profile indices (total cholesterol (TC), triglycerides (TGs), high-density lipoprotein cholesterol (HDL-C), and low-density lipoprotein cholesterol (LDL-C)), fMRI screens and scale assessments for the participants to select the patients to be included. For outpatients who meet the inclusion and exclusion criteria and wish to participate in the study, we will fully communicate with patients and their family members face-to-face about the trial to ensure that the patients are able to participate throughout the study.

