### Inclusion criteria

Eligible participants for DCI subjects should meet the following inclusion criteria: (1) the 2020 American Diabetes Association Standards of Medical Practice for diabetes with a duration of ≥ 2 years; (2) signs or symptoms of memory loss; (3) Montreal Cognitive Assessment Scale (MoCA) score < 26 points, Clinical Dementia Rating (CDR) ≥ 0.5 points; (4) activities of daily living (ADLs) not significantly affected, and instrumental ability of daily living (IADL) score ≥ 16 points; (5) aged 50–70 years, with more than 6 years of education, able to complete a cognitive assessment; (6) sufficient visual and auditory discrimination to undergo neuropsychological testing; (7) no evidence of infection, infarction, or other focal injury, or associated clinical symptoms, as detected by transcranial CT or MRI in the 12 months prior to screening; allows for white matter lesions or cavitary infarcts in noncritical brain regions without affecting the subject’s cognitive function; and (8) signed informed consent, volunteered to participate in the study, and were able to cooperate with the physician in completing the clinical study. Eligible participants who meet the following inclusion criteria as healthy subjects: (1) conditions such as age and education that are comparable to other groups of subjects; (2) absence of significant neurological foci and absence of associated disorders that could cause cognitive impairment, as determined by cranial MRI; (3) no religious beliefs, no bad habits, such as tobacco, alcohol, coffee, and tea; (4) no job or life stress during the observation period; (5) in good health, free of cardiovascular and other organic diseases; (6) total MoCA score ≥ 26 points; and (7) signed informed consent, volunteered to participate in the study, and were able to cooperate with the physician in completing the clinical study.

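### Within-arm paired t tests on MoCA are biased towards improvement by selection at MoCA below 26, and the valid between-arm test of changes gives up some precision by not adjusting for baseline

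*Protocol article*

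**What the plan says.** Under Clinical data analysis the protocol article fixes three uses of the clinical data.

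- Within groups: "A paired *t* test will be used to compare the clinical outcomes within the groups".
- Between groups: "Analysis of variance and the Wilcoxon rank-sum (if normality is violated) will be used to compare the clinical feature changes between groups".
- At baseline: "Student’s *t* test and the chi-square test will be used to compare group differences at baseline". This is the only use of baseline as a value in its own right. No covariate is named.

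The threshold is common to all of them: "All statistical tests will be bilateral, and *p* < 0.05 will be considered statistically significant". The Abstract announces inter- and intragroup analyses without ranking them.

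On selection, the Participants section says that pre-treatment work-up includes "scale assessments for the participants to select the patients to be included", and the Inclusion criteria require "Montreal Cognitive Assessment Scale (MoCA) score < 26 points" of the patients and 26 or more of the healthy subjects. Setting of the study describes days -3 to 0 as a period for both baseline and selection. The Discussion counts one evaluation before treatment, two during it and four in follow-up. MoCA is among the primary outcomes and is the basis of the sample size.

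**The concern.** A score used to admit patients only when it is low tends to be higher on retest, whatever the treatment, as long as the retest correlation is below 1. Only one pre-treatment evaluation is described, so the selecting score and the baseline score are the same. A paired t test in the electroacupuncture arm therefore tests treatment effect plus this drift, plus any practice effect from repeated testing. The sham arm is there to remove such components, and a within-arm p-value bypasses it. Because the plan ranks neither analysis, a significant paired test could be reported as benefit.

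The between-arm test has a different and smaller problem. It subtracts baseline in full rather than adjusting for it, which costs precision in a trial planned on about 24 evaluable patients per arm.

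**Working it through.** **The plan's own figure.** Sample size estimation gives n of about 24, raised for 20% dropout: 24 / (1 - 0.20) = 30 per group, which reproduces. The 24 itself cannot be checked because no SD is given. That is a separate matter, and nothing below depends on it except as the choice of n = 24 or 30.

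**Inputs.** From the article: selection at MoCA < 26, n = 30 (24 evaluable), two-sided 0.05, hence 2.5% in the direction of improvement. Assumed, because the article gives none: source-population mean μ = 23 to 25, SD σ = 3 to 3.5, retest correlation ρ = 0.7 to 0.9, equal mean and SD at retest, approximate normality.

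**(a) Paired test with no treatment effect.** Let a = (26 - μ)/σ and λ = φ(a)/Φ(a).

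- Spurious gain = (1 - ρ)σλ.
- Baseline variance among those selected: v = σ²(1 - aλ - λ²).
- Variance of the change = (1 - ρ)²v + σ²(1 - ρ²).
- Chance of a significant improvement: noncentral t with n - 1 degrees of freedom and noncentrality (gain / SD of change)√n.

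The two ends of the grid:

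| μ, σ, ρ | λ | gain | v | SD of change | n = 30 | n = 24 |
|---|---|---|---|---|---|---|
| 23, 3, 0.9 | 0.288 | 0.1 × 3 × 0.288 = 0.09 | 5.67 | √(0.01 × 5.67 + 9 × 0.19) = 1.33 | 5% | 5% |
| 25, 3.5, 0.7 | 0.625 | 0.3 × 3.5 × 0.625 = 0.66 | 5.27 | √(0.09 × 5.27 + 12.25 × 0.51) = 2.59 | 27% | 22% |

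Every cell between them exceeds 2.5%. Placing the cut at 25.5, because scores are integers, gives 6 to 33% at n = 30. Wider assumptions (mean 23 to 26, SD 2 to 4, ρ 0.6 to 0.9, cut 25.5) give gains of 0.04 to 1.41 points and 4 to 69%. Practice effects are not included.

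**(b) Between-arm test of changes.** In a simulation with no treatment effect (4000 runs, n = 30 per arm), ANOVA of changes for electroacupuncture versus sham rejected in 4.7 to 5.7% of runs, so its size is right. For precision, the ratio of ANCOVA to change-score variance is

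σ²(1 - ρ²) / [(1 - ρ)²v + σ²(1 - ρ²)].

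Without truncation v = σ² and this reduces to (1 + ρ)/2. With baseline truncated at 26, over the same μ and σ:

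- lowest, at μ = 23, σ = 3, ρ = 0.5: 6.75 / (0.25 × 5.67 + 6.75) = 0.83;
- highest, at μ = 25, σ = 3.5, ρ = 0.9: 2.3275 / (0.01 × 5.27 + 2.3275) = 0.98;
- for ρ = 0.7 to 0.9 alone: 0.90 to 0.98.

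The equivalent gain in patients runs from 1/0.98 - 1 = 2% to 1/0.83 - 1, about 21%.

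**Healthy group.** Subjects admitted at MoCA ≥ 26 regress downwards while patients regress upwards. With an assumed healthy-group mean of 27 and SD of 1.5, a three-group ANOVA of changes rejected in 9 to 33% of simulated runs with no treatment effect.

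**The case against.** The best defence is that the plan already contains a valid test. Regression to the mean and practice act equally on the two randomized arms, so comparing their changes is unbiased. The sham arm was added for exactly this kind of reason, and nothing makes the paired test the efficacy test. That stands. A reader might infer that the planned analysis as a whole shows improvement where there is none. The document does not support that reading: the false improvement belongs to the within-group tests only, or to a three-group ANOVA if the healthy subjects enter it.

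A reader might also apply (1 + ρ)/2 and claim that 11 to 33% more patients are being wasted for ρ of 0.5 to 0.8. That formula assumes an untruncated baseline, which contradicts the selection argument. The smaller range above is the consistent one.

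Nor can the plan be faulted for ignoring a stratification factor. Study design says only that patients are "randomized and stratified according to the clinical treatment". No baseline factor is named there or in the randomization section, and the phrase may simply mean treatment group.

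Finally, covariates, repeated-visit models and normality rules are often left to an analysis plan, this is a condensed article of a pilot trial, and the visit timetable for each outcome is in a figure not available here. Details of that kind are therefore not counted as omissions. The point rests on what the article itself fixes: paired tests within groups and unadjusted changes between them.

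**Conclusion.** The point holds in two separate parts. The within-arm paired test on MoCA is biased towards improvement. The direction follows from selecting and measuring baseline at the same evaluation, for any retest correlation below 1. The size, about 0.1 to 0.7 points and 5 to 27% false improvement at n = 30 (5 to 22% at n = 24), rests on the assumed mean, SD and correlation and could lie outside that range. The electroacupuncture versus sham comparison of changes is valid, and its shortcoming is a modest loss of precision (variance ratio 0.83 to 0.98 for correlations of 0.5 to 0.9). This does not undermine the trial. It is a stated method that should be improved, chiefly because the plan does not put the valid comparison ahead of the biased one.

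**What to change.** - State that the main clinical analysis is electroacupuncture versus sham on MoCA at week 8, adjusted for baseline MoCA by ANCOVA or a mixed model for repeated measures, reported as a difference with 95% confidence interval.
- Keep the healthy group out of that treatment-effect test and use it for descriptive or cross-sectional comparison.
- Report within-group changes descriptively, without p-values.
- Clarify what the stratification in Study design refers to, and add it as a covariate only if it proves to be a real baseline factor.

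The cost is wording in the analysis section. No new data are needed, and the expected precision is somewhat better than under the current plan.

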### Setting of the study

This clinical trial will be conducted at the third Affiliated Hospital of Changchun University of Chinese Medicine (Changchun, China). Eligible participants will be randomly assigned to the intervention group (*n* = 60) and the control group (*n* = 30). The intervention group will be divided into the “Adjust Zang-fu and Arouse Spirit” electroacupuncture group (*n* = 30) and sham electroacupuncture group (*n* = 30). The total observation period will include a − 3~0-day baseline selection period, an 8-week treatment period, and a 6-month follow-up period. They will receive 40 sessions of electroacupuncture or sham electroacupuncture treatment over 8 weeks (five sessions per week). Assessments will be conducted at baseline and at 4 and 8 weeks after randomization, as well as at 1, 2, 3, and 6 months after treatment. Figure 1 illustrates the study flowchart. This protocol will be reported according to the SPIRIT 2013 [17] statement of recommendations for intervention trials: Defining Standard Protocol Items for Clinical Trials. The trial process was designed according to the STRICTA 2015 [18] report (Table 1).

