### Withdrawal criteria

Participants meeting any of the following criteria will be withdrawn by the unanimous decision of the two researchers: (1) participant’s decision to drop out of the study at any time for any reason; (2) death or other major adverse events or accidents occur due to disease development; (3) participants display poor compliance with the clinical trial protocols, an unwillingness to continue in the study, or requests to withdraw from the study; and (4) participants are noncompliant with the prescribed treatment, are not treated as prescribed, or have incomplete observation data affecting the evaluation.

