#### Neuroimaging data analysis

Neuroimaging data processing and statistical analysis were carried out by the individualized Neuroimaging Research Laboratory of Martinos Neuroimaging Center, Massachusetts General Hospital, Harvard Medical School, USA.

The structural MRI data will be analyzed using the VBM toolbox within SPM12. The steps include interlayer time difference correction, spatial difference correction, head motion correction, standardization, and Gaussian smoothing. In the head motion correction process, the images of the subjects whose translation is less than 1 mm and rotation movement is less than 2° will be involved in the follow-up analysis. The fMRI data will be analyzed using the CIVET-pipeline toolbox and SurfStat in MATLAB 2018b. The steps include removing high-frequency components by a bandpass filter, removing the average signal of the whole brain and the signals of the ventricle and white matter, and then registering the data to the surface space of FreeSurfer. T tests and repeated-measures analysis of variance will be conducted to investigate the differences in brain regions in each group. Pearson correlation analysis will be used to test the correlation between fMRI data and clinical variables. According to the results of MRS scanning, the concentration of target metabolites will be statistically analyzed. A paired *t* test will be used to compare within the groups. Analysis of variance and the Wilcoxon rank-sum (if normality is violated) will be used to compare between groups.

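### As written, secondary clinical outcomes are compared by unadjusted change scores among patients seen at each visit, so unequal response-related dropout would bias them, and baseline and earlier visits go unused

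*Protocol article*

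**What the plan says.** All places are in the protocol article.

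- **Clinical data analysis, within groups.** A paired t "test will be used to compare the clinical outcomes within the groups".
- **Clinical data analysis, between groups.** "Analysis of variance and the Wilcoxon rank-sum (if normality is violated) will be used to compare the clinical feature changes between groups".
- **Clinical data analysis, missing values.** "Missing data for the primary outcome will be imputed using the multiple imputation method". No rule is stated for the other outcomes.
- **Neuroimaging data analysis.** This is the only place that names a repeated-measures method: "T tests and repeated-measures analysis of variance will be conducted to investigate the differences in brain regions in each group".
- **Setting of the study.** Assessments fall "at baseline and at 4 and 8 weeks after randomization, as well as at 1, 2, 3, and 6 months after treatment". The Discussion counts one before, two during and four after treatment, "for a total of seven evaluations".
- **Sample size estimation.** The loss is put at 20 per cent ("the shedding rate was 20"), with no split by arm.
- **Withdrawal criteria.** Criterion 4 covers noncompliant participants and those who "are not treated as prescribed, or have incomplete observation data affecting the evaluation".
- **Secondary outcomes.** HbA1c, four lipid measures and IADL are outcomes in the usual sense. HIS, SAS and SDS are described as tools for excluding patients.

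**The concern.** A change score needs both of its values. A patient with baseline and week-4 values but no week-8 value contributes nothing to the week-8 comparison of an unimputed outcome, although the week-4 value is on file. The rank-sum fallback is a test for independent groups, so the natural reading of the ANOVA is a one-way comparison of changes. The article names a repeated-measures analysis where it wants one, and does so only for brain regions.

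Two things are at stake. The first is bias. If patients doing poorly on sham leave, the remaining sham patients look better and the treatment effect is understated; if they leave the active arm, it is overstated. The withdrawal rule for noncompliance or incomplete data makes response-related loss more plausible. The second is precision. ANOVA of changes does not adjust for baseline, which costs precision at 30 per arm even if nobody leaves.

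**Working it through.** **1. The plan's own figure.** The target is about 24 per group before loss. 24 / (1 - 0.20) = 30 per group, so the dropout allowance reproduces. In a group of 30, 20% is 6 patients.

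**2. Assumptions not in the document.** Outcome SD 1; equal correlation rho = 0.5-0.7 between visits; measurements at baseline, week 4 and week 8; and the split and mechanism of dropout. The results below are therefore ranges.

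**3. Bias by formula.** Suppose the 20% of one arm with the worst week-4 change leave.
- Removing the lowest 20% of a normal variable raises the mean of the rest by 0.35 SD.
- Correlation of the week-4 and week-8 changes: (1 - rho) / [2(1 - rho)] = 0.5, whatever rho is.
- Bias of the week-8 change comparison: 0.35 x 0.5 = 0.175 SD of the change score.
- In outcome SDs, multiply by sqrt[2(1 - rho)]: 0.175 x 1.00 = 0.175 at rho 0.5, and 0.175 x 0.775 = 0.136 at rho 0.7. A true effect of 0.5 lost through sham dropout would appear as 0.32-0.36.

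**4. Simulation, 30 per arm, no true effect, 4,000 runs per case.** Bias is in SDs of the change score. Ranges cover rho 0.5 and 0.7, and strict or probabilistic selection of who leaves.

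| Loss by arm | Dropout depends on | Bias, observed cases | Type I error (nominal 0.05) | Bias after joining visits |
|---|---|---|---|---|
| 20% / 0% | observed week-4 change | 0.13-0.18 | 0.08-0.10 | at most 0.01 |
| 30% / 10% | observed week-4 change | 0.11-0.15 | 0.08-0.09 | at most 0.01 |
| 20% / 20% | observed week-4 change | about 0 | 0.05-0.06 | about 0 |
| 20% / 0% | unseen final change | 0.24-0.34 | 0.16-0.28 | 0.17-0.27 |

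The 20% / 0% rows average 10% loss over the two arms. The 30% / 10% row keeps the average at the protocol's 20%.

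**5. What each remedy recovers.** Large-sample check with a true effect of 0.5 outcome SD, 20% lost from sham only on the week-4 change, rho 0.5-0.7:
- ANOVA of observed changes: about 0.32-0.36.
- ANCOVA on baseline, without week 4: about 0.40.
- Model joining the visits: 0.50.

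**6. Precision from baseline adjustment alone.** The ratio of standard errors, ANCOVA to change score, is sqrt[(1 - rho^2) / (2(1 - rho))] = sqrt[(1 + rho) / 2]. This is sqrt(0.75) = 0.866 at rho 0.5 and sqrt(0.85) = 0.922 at rho 0.7, so the standard error is about 8-13% smaller.

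**The case against.** A reader might infer that all secondary outcomes are analysed on completers and are therefore biased. The document does not support that, for four reasons.

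- **Observed at the visit is not the same as completing the study.** Loss during the 6-month follow-up leaves the week-8 comparison untouched. An unseen analysis plan may also add a rule for secondary outcomes. The point therefore rests on the tests that the article does fix, not on its silence.
- **Unequal dropout is not predicted.** The article gives one overall rate. Patients cannot feel HbA1c or lipids, they are not told their assignment, and glucose is kept stable in both arms. If dropout follows some other measure correlated r with the outcome (an assumption), a bias of 0.14-0.16 outcome SD (rho 0.6-0.7) shrinks to 0.07-0.08 at r = 0.5 and about 0.03 at r = 0.2.
- **The visit schedule for each outcome is not confirmed.** The timetable figure is not shown, and the Abstract mentions assessment only at baseline and before and after treatment. If laboratory values have no week-4 measurement, there is no intermediate value to use.
- **Not every listed secondary outcome is affected.** HIS, SAS and SDS serve as exclusion tools.

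It would also be too strong to call multiple imputation for MoCA a mistake. With intermediate visits in the imputation model it rests on the same missing-at-random assumption as a mixed model, and choosing between them is a matter of preference.

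These objections limit the size and reach of the point. What stands is that the stated tests use neither baseline adjustment nor earlier visits, and that the one stated missing-data rule stops at the primary outcome.

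**Conclusion.** The concern holds in a conditional form. The clinical section fixes a method that leaves HbA1c, lipids and IADL open to bias if loss is unequal between arms and related to response. The size is up to about 0.13-0.18 SD of the change score when 20% of one arm leaves on values already observed, and 0.11-0.15 SD at 30% versus 10%. It is about zero with equal loss by the same mechanism.

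A joint model removes the bias only when dropout depends on observed values and intermediate measurements exist. When dropout depends on unseen values, 0.17-0.27 SD of a 0.24-0.34 SD bias remains. The precision loss from omitting baseline does not depend on dropout. The correlations, dropout splits and mechanisms are assumptions. In a pilot whose primary outcome already has a principled method, this is a worthwhile and cheap improvement, not a fatal flaw.

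**What to change.** For the randomized comparison of electroacupuncture with sham:

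1. Analyse each continuous clinical outcome that has more than one post-baseline visit with a mixed model over all its scheduled visits. Include arm, visit, arm by visit and the baseline value, with a pre-specified covariance structure. Read the difference at end of treatment from this model.
2. For outcomes measured only before and after treatment, replace ANOVA of changes with ANCOVA on the baseline value. State that this gains precision but removes only part of any dropout bias.
3. Multiple imputation may remain the primary handling for MoCA, provided the imputation model includes the intermediate visits.

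The cost is analysis wording and a little more programming. It needs no extra patients or visits, and the model is available in the stated software. The small downside is that a covariance structure must be chosen in advance.
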